## Abstract

**Background::**

The morbidity and mortality of acute myocardial infarction are on the rise, and the efficacy of conventional treatment is limited. Shexiang Baoxin Pill is a kind of proprietary Chinese medicine, which has been widely used in the treatment of acute myocardial infarction in China, and has certain advantages. At present, there is a lack of strict randomized controlled trials to verify the efficacy and safety of Shexiang Baoxin Pill combined with Western medicine in the treatment of acute myocardial infarction. Therefore, the purpose of this randomized controlled trial is to evaluate the clinical efficacy of Shexiang Baoxin Pill combined with Western medicine in the treatment of acute myocardial infarction.

**Methods::**

This is a prospective randomized controlled trial to study the efficacy and safety of Shexiang Baoxin Pill combined with Western medicine in the treatment of acute myocardial infarction. It is approved by the Clinical Research Society of our hospital. According to 1:1, the patients will be randomly divided into observation group (Shexiang Baoxin Pill combined with Western medicine group) and control group (routine Western medicine group). The patients in the 2 groups will be treated continuously for 4 weeks and followed up for 3 months. Pay attention to its curative effect index and safety index. The observation indexes included total effective rate of improvement of cardiac function, left ventricular ejection fraction (LVEF), endothelin (ET), nitric oxide (NO) level, interleukin-6 (IL--6), adverse reactions, and so on. We will analyze the structure by SPSS version 19.0.

**Discussion::**

This study will evaluate the efficacy and safety of Shexiang Baoxin Pill combined with Western medicine in the treatment of acute myocardial infarction. The results of this experiment will provide clinical basis for Shexiang Baoxin Pill combined with Western medicine in the treatment of acute myocardial infarction.

**Trial registration::**

OSF Registration number: DOI 10.17605/OSF.IO/PYJTK.

## Introduction

1

Acute myocardial infarction (AMI) refers to a sharp decrease or complete interruption of coronary artery blood supply caused by various reasons, resulting in serious and lasting acute myocardial ischemia leading to cardiomyocyte necrosis.^[1]^ It is the most serious manifestation of coronary artery disease and is also one of the main causes of death in patients with coronary heart disease.^[2]^ With the change of lifestyle and the increasing degree of population aging, its morbidity and mortality are increasing year by year, bringing a heavy burden to individuals, families, and society.^[3]^ Typical clinical manifestations are severe pain in the precordial region, suffocation with sweating, and pain is not easy to relieve, can be complicated with cardiogenic shock, arrhythmia or heart failure, the disease develops rapidly, often life-threatening, and the prognosis is poor.^[4]^ Therefore, timely and effective treatment of AMI is the key to reduce the mortality and disability rate.

The morbidity and mortality of AMI are increasing year by year, and percutaneous coronary intervention (PCI) is an effective treatment for the disease. In addition, it also includes thrombolysis, anticoagulation, anti-platelet aggregation, improving ventricular rate, preventing ventricular remodeling, and enhancing myocardial energy metabolism.^[5,6]^ At the same time, traditional Chinese medicine also plays an important role in its prevention and treatment.^[7]^ Shexiang Baoxin Pill is a traditional Chinese medicine preparation commonly used in the clinical treatment of AMI in China. In 1993, it was listed as one of the emergency essential drugs by the State Administration of traditional Chinese Medicine.^[8]^ Shexiang Baoxin Pill is also recommended for the treatment of AMI patients in the “consensus of experts on diagnosis and treatment of Acute Myocardial Infarction with Integrated traditional Chinese and Western Medicine” issued by the Cardiovascular Professional Committee of Chinese Society of Integrated traditional Chinese and Western Medicine in 2018. Shexiang Baoxin Pill is composed of artificial musk, Storesin, toad, artificial bezoar, cinnamon, borneol, and ginseng extract, which can relieve chest pain, inhibit platelet aggregation in patients with AMI, reduce blood lipids, improve vascular endothelium and cardiac function, and has good safety.^[9]^ At present, it has been proved that it has satisfactory clinical efficacy and high safety in the treatment of cardiovascular diseases such as chronic heart failure, coronary heart disease and acute coronary syndrome.^[10–13]^ Although Shexiang Baoxin Pill has been used in clinic, there is still a lack of strict randomized controlled trials to study the efficacy and safety of Shexiang Baoxin Pill combined with Western medicine in the treatment of myocardial infarction. Therefore, we intend to use this randomized controlled trial to evaluate the clinical efficacy of Shexiang Baoxin Pill combined with Western medicine in the treatment of AMI.

## Materials and methods

2

### Study design

2.1

This is a prospective, double-blind randomized controlled trial to study the efficacy and safety of Shexiang Baoxin Pill combined with Western medicine in the treatment of AMI. This experiment will follow the comprehensive trial reporting standard.^[14]^ The flow chart is shown in Figure 1.

**Figure 1 F1:**
[figure not shown]
Flow diagram.

### Ethics and registration

2.2

This research scheme is in line with the Helsinki Declaration and approved by the Clinical Research Ethics Committee of our hospital. This laboratory is already registered in the open science framework (OSF) (registration number: DOI 10.17605/OSF.IO/PYJTK). Before randomly grouping, all patients are required to sign a written informed consent form. Participants can withdraw from the study at any time for any reason. After withdrawal, the patient's data will be used with the patient's consent.

### Patients

2.3

(1)Inclusion criteria: ① meet the diagnostic criteria of AMI, and diagnosed by clinical manifestations, myocardial markers, electrocardiogram and other auxiliary examination; ② onset time is within 24 hours, taking nitrate drugs cannot be relieved; ③ the age is 30 to 80 years; ④ there is no Shexiang Baoxin pill and other related drugs within 3 months before admission; ⑤ voluntary subjects, sign informed consent, good compliance.(2)Exclusion criteria: ① patients with heart failure induced by other diseases such as congenital heart disease; ② patients with malignant tumors or other liver, kidney, and lung diseases; ③ patients with other heart diseases such as severe arrhythmia; ④patients with severe mental illness; ⑤ patients with allergies or contraindications to medication in this study.

### Randomization and blinding

2.4

Randomly grouped by independent statisticians, random sequences are generated using SAS V.9.4 software, and the numbers are stored in opaque envelopes. One hundred twenty patients will be randomly divided into observation group and treatment group according to the rate of 1:1. The allocation of research by attending physicians, patients, assistant researchers, data statistical analysts, and nurses is unknown throughout the study.

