### Data collection and management

2.7

The data will be collected according to the evaluation criteria before the beginning of treatment, 72 hours after the beginning of treatment and at the end of treatment. Each patient will be followed up by outpatient or telephone within 3 months after the end of treatment, and the reasons for the loss of follow-up cannot be collected in detail. All data will be collected jointly by 1 or 2 assistants. Personal information about potential participants and registered participants will be collected, shared, and stored in a separate storeroom to protect before, during, and after the test confidentiality. Access to the database is limited to the researchers of this research group.

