### Statistical analysis

2.8

The data will be processed by SPSS19.0 statistical software, the measurement data will be expressed by $\bar{x}\pm s$, *t* test, counting data will be expressed by rate (%), and *χ*^2^ test will be used. When *P <* .05, the difference is statistically significant.

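### The primary total effective rate is compared by an unadjusted chi-square test although baseline values such as LVEF are collected: valid on average, but precision is given up

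*Protocol article*

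**What the plan says.** - **Test.** Section 2.8 assigns the t test to continuous data. For rates it says "counting data will be expressed by rate (%), and *χ*^2^ test will be used", with the criterion "When *P <* .05, the difference is statistically significant". No covariate enters either test.
- **Primary outcome.** Section 2.6 makes the "total effective rate of improvement of cardiac function" the main outcome (the words are those of the abstract). It is graded from ECG and symptoms in three categories. As a rate, it falls under the chi-square test.
- **Size and allocation.** Section 2.4 says "One hundred twenty patients will be randomly divided into observation group and treatment group according to the rate of 1:1", so 60 per arm, and "random sequences are generated using SAS V.9.4 software, and the numbers are stored in opaque envelopes". It neither describes nor rules out blocks or strata.
- **Baseline data.** Section 2.7 says "The data will be collected according to the evaluation criteria before the beginning of treatment", and again at 72 hours and at the end of treatment. The criteria in section 2.6 include ECG, symptoms, LVEF, ET, NO, IL-6 and CRP.
- **Population.** Section 2.3 admits acute myocardial infarction "diagnosed by clinical manifestations, myocardial markers, electrocardiogram and other auxiliary examination", at ages 30 to 80 and with onset in the preceding 24 hours.

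**The concern.** Patients who enter with better cardiac function can be expected to do better on an ECG and symptom grade whichever arm they are in. A test that ignores this treats the predictable part of the outcome as noise.

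Two things follow. Power is lower than the same data could give. And if the arms happen to differ at baseline, the difference passes into the primary result uncorrected. With 60 per arm neither is negligible when the covariate is truly prognostic, and the baseline value is to be collected anyway.

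**Working it through.** **Inputs.** From the article: 120 patients, 60 per arm, chi-square test, significance level 0.05. Assumed, because the article gives no figures: a two-sided test, the success rates, and the strength of the covariate. The stated 120 cannot be reproduced without a control rate, effect and power. A condensed article may leave those out, and nothing here depends on them.

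**1. Power of the stated test.** With pooled rate p̄ and 60 per arm, power = Φ[(Δ − 1.96·√(2p̄(1−p̄)/60)) / √((p₁(1−p₁)+p₂(1−p₂))/60)].

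- 70% vs 90%: (0.20 − 1.96 × 0.0730)/0.0707 = 0.80, power 79%.
- 75% vs 90%: (0.15 − 1.96 × 0.0694)/0.0680 = 0.21, power 58%.

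**2. Chance imbalance.** Take a factor present in half the patients and allocation without stratification. The difference in counts between arms, plus 60, is Binomial(120, 0.5) with SD √30 = 5.48.

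- 10 points or more (6 patients): 31.5%.
- 15 points or more (9 patients): 12.0%.

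**3. Type I error with a binary factor** (200,000 simulated trials per scenario). Averaged over all randomisations, the chi-square test rejects in 4.97% to 5.24%. Among trials with an imbalance of 15 points or more, it rejects in 7.4% (success 90% vs 70% by factor level), 10.0% (95% vs 65%) or 14.4% (95% vs 50%). A Cochran-Mantel-Haenszel test stays at 4.6% to 5.3%. The other trials compensate: with 5% overall, the last case implies (5 − 0.12 × 14.4)/0.88 = 3.7% in the remaining 88%.

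**4. Power with a binary factor**, common treatment odds ratio 3.86 (overall about 70% vs 87% to 89%):

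| Success by factor level | Odds ratio of factor | Chi-square | Stratified test | Gain |
|---|---|---|---|---|
| 85% / 55% | 4.6 | 75.6% | 78.2% | 2.6 |
| 90% / 50% | 9 | 71.2% | 76.6% | 5.4 |
| 95% / 45% | 23 | 65.4% | 74.4% | 9.0 |

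With a weak factor (75% / 65%, odds ratio 3.00/1.86 = 1.6) the gain is nil.

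**5. Power with a continuous covariate**, closer to LVEF (10,000 simulated trials per scenario). The log-odds slope is b per SD. The chi-square test is compared with the likelihood-ratio test for arm in a logistic model that contains the covariate.

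| b | AUC, about | 70% vs 90% | Gain | 75% vs 90% | Gain |
|---|---|---|---|---|---|
| 0 | 0.50 | 80.1% → 81.0% | 0.9 | 58.1% → 60.2% | 2.1 |
| 0.5 | 0.63 | 80.8% → 82.6% | 1.9 | 59.1% → 62.5% | 3.4 |
| 1.0 | 0.74 | 80.4% → 85.9% | 5.5 | 58.1% → 65.1% | 7.0 |
| 1.5 | 0.82 | 80.7% → 90.0% | 9.3 | 59.1% → 72.3% | 13.3 |
| 2.0 | 0.87 | 80.2% → 93.0% | 12.8 | 58.8% → 77.1% | 18.3 |

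The row b = 0 shows that 1 to 2 points come from the change of test, not from the covariate. Net of that, the weak covariate (b = 0.5) contributes 1.9 − 0.9 = 1.0 and 3.4 − 2.1 = 1.3 points. Type I error at 75% vs 75% is 5.0% to 5.4% for both tests.

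**6. Can the model be fitted?** At 70% vs 88% the expected failures are 60 × 0.30 + 60 × 0.12 = 25. That is about 12 per term with arm and LVEF, and about 8 with a third term, so there is no room for a long covariate list.

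**The case against.** The best defence is that section 2.8 is a very short summary, that an article may leave covariates to a full protocol or SAP, and that a chi-square test for rates is no error. The last part stands. The first does not dispose of the point: the article names a test for rates, so an adjusted primary analysis would replace what is stated, not fill a gap.

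It is also fair to say that the larger gains rest on strong covariates. The factor odds ratios of 9 and 23 are steep, and the gain is small or nil with a weak predictor.

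Several stronger readings are tempting, and the document does not support them:

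- **The test is biased or has inflated error.** It is not. The raised rates in step 3 hold only given an imbalance, and they average out to about 5%.
- **Allocation is unstratified.** Section 2.4 is silent, and silence in an article is no finding. The imbalance figures apply to factors that were not stratified on.
- **Strong predictors are in hand.** Nothing in the article says how well LVEF or any other item predicts the outcome. That it predicts at all is a clinical inference.
- **Infarct type can be used as a covariate.** An ECG is needed for diagnosis, but infarct type is not a named data item.

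Section 2.6 does not say which of the three grades count as success. That needs settling in its own right, but the point holds under either pooling.

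**Conclusion.** The point holds as one of efficiency and of protection against chance imbalance, not of validity. Section 2.8 states an unadjusted test for the primary outcome, while sections 2.6 and 2.7 together put a baseline LVEF in the data set. Adjustment would cost almost nothing and keep type I error near 5%. It would add about 0 to 3 points of power for a weak to moderate covariate, and about 5 to 9 points or more for a strong one. At 60 per arm, where the stated test has 79% power for 70% vs 90% and 58% for 75% vs 90%, that is worth having.

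The size rests on assumed success rates, a two-sided 5% level and an assumed covariate strength, none of which the article gives. That LVEF is measured before treatment is read from sections 2.6 and 2.7 together.

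**What to change.** In section 2.8, replace the chi-square test as the primary comparison of total effective rate with one prespecified analysis:

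- A logistic model with arm and baseline LVEF, and at most one other recorded baseline variable, such as age.
- A standardised risk difference with 95% CI from the same model. State in advance that the test of the arm term carries the decision, because near the 5% limit it and the interval can disagree.
- The plain chi-square test as a sensitivity analysis.
- No switch of the primary test according to what the data look like, for instance to a stratified test when failures are few.

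The cost is a few sentences. The covariates must be fixed before unblinding, and a rule is needed for missing baseline LVEF so that no randomised patient drops out of the primary analysis for that reason. No stratified randomisation, new patients, visits or measurements are required.

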### Study design

2.5

After admission, patients in both groups will be given routine treatment, and electrocardiogram, blood pressure and blood oxygen saturation will continuously be monitored. Each patient inhaled oxygen with low flow for 3 days, and each patient will be told to rest in bed according to his or her own condition. Seventy-five milligram, qd of hydroxyclopidogrel sulfate, 100 mg, qd of aspirin enteric-coated tablets and 20 mg, qn of Atto vastatin calcium tablets will be taken orally.

The observation group will be treated with 67.5 mg, tid of Shexiang Baoxin Pill on the basis of routine treatment, while the control group will be treated with placebo instead of Shexiang Baoxin Pill. The appearance, texture, and smell of the placebo will be consistent with those of Shexiang Baoxin Pill. The attending physician can adjust the medication according to the specific conditions of the patient, and all schemes will be recorded in detail for final result analysis.

During the treatment period, the distribution of drugs will be distributed to the corresponding numbered patients by nurses who do not know about the grouping according to the drug number.

### Evaluation criteria and efficacy judgment

2.6

(1)Main outcome indicators: ①Total effective rate of improvement of cardiac function (refer to the principle of clinical research on treating heart failure with new Chinese Medicine),^[15]^ effective: ECG is stable, clinical symptoms basically disappear; improvement: ECG is basically stable, clinical symptoms are improved; ineffective: clinical symptoms, ECG do not change or aggravate.(2)Secondary outcome index: left ventricular ejection fraction (LVEF), endothelin (ET), nitric oxide (NO) level, interleukin-6 (IL--6), C-reactive protein (CRP).(3)Adverse reactions: including abnormal liver and kidney function and any uncomfortable symptoms during treatment (such as arrhythmia, digestive tract reaction, etc).

### Data collection and management

2.7

The data will be collected according to the evaluation criteria before the beginning of treatment, 72 hours after the beginning of treatment and at the end of treatment. Each patient will be followed up by outpatient or telephone within 3 months after the end of treatment, and the reasons for the loss of follow-up cannot be collected in detail. All data will be collected jointly by 1 or 2 assistants. Personal information about potential participants and registered participants will be collected, shared, and stored in a separate storeroom to protect before, during, and after the test confidentiality. Access to the database is limited to the researchers of this research group.

### Statistical analysis

2.8

The data will be processed by SPSS19.0 statistical software, the measurement data will be expressed by $\bar{x}\pm s$, *t* test, counting data will be expressed by rate (%), and *χ*^2^ test will be used. When *P <* .05, the difference is statistically significant.

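### Five continuous secondary outcomes get a plain t test although a pre-treatment value is planned for each; adjusting for that value would tighten the comparison with data already scheduled

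*Protocol article*

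**What the plan says.** Section 2.8 (Statistical analysis) gives one rule for continuous data: "the measurement data will be expressed by" mean and standard deviation, with a t test. Count data get a chi-square test, and the significance threshold is .05. No covariate or adjusted model is mentioned anywhere in the article. Section 2.8 does not say whether the t test is applied to final values or to changes from baseline.

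The continuous outcomes are the five in section 2.6: "Secondary outcome index: left ventricular ejection fraction (LVEF), endothelin (ET), nitric oxide (NO) level, interleukin-6 (IL--6), C-reactive protein (CRP"). The main outcome, the "total effective rate of improvement of cardiac function", is categorical and falls under the chi-square test.

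Section 2.7 (Data collection and management) gives the schedule on which measurements are "collected according to the evaluation criteria before the beginning of treatment, 72 hours after the beginning of treatment and at the end of treatment". A pre-treatment value is therefore planned for each of the five.

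On size, section 2.4 states: "One hundred twenty patients will be randomly divided into observation group and treatment group according to the rate of 1:1". That is 60 per arm.

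**The concern.** A test that takes no account of a baseline correlated with the outcome leaves explainable variation in the error term. A t test on change does use the baseline, but fixes its coefficient at 1, which is generally not the most efficient weight. Either way, the confidence intervals for LVEF and the four markers are likely to be wider than the planned data allow. With 60 per arm, a moderate effect on a secondary outcome could be missed for that reason alone.

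This is a question of the method that the article names, not of a detail left out of it. Section 2.8 commits to the t test, and the data for a more precise analysis are already scheduled in section 2.7.

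**Working it through.** **Inputs from the protocol article.** Total 120 at 1:1, so n = 60 per arm (section 2.4). Threshold 0.05 (section 2.8), taken as two-sided because the side is not stated. Baseline, 72-hour and end-of-treatment measurements (section 2.7). The article gives no effect size, SD or power behind 120, so there is no planned calculation to reproduce.

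**Assumptions.** Treatment effect 0.5 SD; the same SD σ at baseline and at the end of treatment; no dropout; correlation ρ between the two values, varied from 0 to 0.7. None of these is in the article.

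**Variance of the between-arm difference, in units of 2σ²/n:**
- t test on final values: 1
- t test on change: 2 − 2ρ
- ANCOVA on baseline: 1 − ρ²

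Hence ANCOVA relative to the final-value t test is 1 − ρ². Relative to the change-score t test it is (1 − ρ²)/(2 − 2ρ) = (1 + ρ)/2.

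| ρ | ANCOVA / final-value t | ANCOVA / change t |
|---|---|---|
| 0 | 1.00 | 0.50 |
| 0.3 | 0.91 | 0.65 |
| 0.5 | 0.75 | 0.75 |
| 0.7 | 0.51 | 0.85 |

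**Cost of estimating the slope.** With N = 120 the ANCOVA variance is inflated by about (N − 3)/(N − 4) = 117/116 = 1.0086. At ρ = 0 this is a loss of about 0.9% against the final-value t test. At ρ = 0.1 it is already offset (0.99 × 1.0086 = 0.9985).

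**Power by normal approximation, effect 0.5 SD.** The standard error of the final-value comparison is √(2/60) = 0.1826 SD. For ANCOVA it is 0.1742, 0.1581 and 0.1304 at ρ = 0.3, 0.5 and 0.7.

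| ρ | final-value t | change t | ANCOVA |
|---|---|---|---|
| 0 | 78.2% | 49.1% | 78.2% |
| 0.3 | 78.2% | 63.9% | 81.9% |
| 0.5 | 78.2% | 78.2% | 88.5% |
| 0.7 | 78.2% | 94.2% | 97.0% |

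Against a change-score test the gains are 81.9 − 63.9 = 18.0, 88.5 − 78.2 = 10.3 and 97.0 − 94.2 = 2.8 points at ρ = 0.3, 0.5 and 0.7.

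**Exact check.** The noncentral t (118 df for the t test; 117 df and the 117/116 inflation for ANCOVA) gives 77.5% for the final-value t test. ANCOVA gives 77.2%, 80.9%, 87.8% and 96.6% at ρ = 0, 0.3, 0.5 and 0.7. In 20,000 simulated trials at each ρ, the ratio of ANCOVA to final-value t variance was 1.009, 0.921, 0.758 and 0.512, in line with the formula.

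**Two other ways to see the size.**
- The difference detectable with 80% power is (1.960 + 0.842) × 0.1826 = 0.511 SD for the final-value t test. Multiplying by √(1 − ρ²) gives 0.488, 0.443 and 0.365 SD for ANCOVA at ρ = 0.3, 0.5 and 0.7.
- In information terms, 120/(1 − ρ²) means that 120 patients under ANCOVA count as about 132, 160 and 235 under the final-value t test.

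**The case against.** **The t test is not wrong.** In a 1:1 randomised trial a between-arm t test is unbiased and holds its error rate. A reader might infer that chance baseline imbalance biases the planned result. It does not: that chance is already inside the 5% error rate. This objection stands, and it makes the point one of efficiency only.

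**The gain is uncertain.** The largest gain, from about 78% to 97%, needs both a test on final values and ρ = 0.7. Section 2.8 states neither. If changes are tested, the gain at ρ = 0.7 is about 3 points. Baselines are taken early in an acute infarction ("onset time is within 24 hours", section 2.3). If they mostly reflect transient timing, ρ may be low and the gain over a final-value test small. This also stands. It limits the size but not the direction, since ANCOVA is at least as precise under either reading apart from the 1% loss near ρ = 0.

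**The source is condensed.** An article may leave the test variable, time point and covariates to a fuller document. That is fair for those details, but the t test itself is stated as the method.

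**Two further inferences are not supported.** One is that hours from onset could be added as a covariate at no cost. The eligibility rule is a threshold, and nothing in the article shows that exact hours are recorded. The other is that before-and-after tests within each arm are planned. Section 2.8 names no such test, and the design is described as a controlled comparison.

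**Conclusion.** The point holds as a precision improvement for the five secondary outcomes. The named t test is valid, but it is not the best use of the baseline values that section 2.7 schedules. Compared with a final-value t test, ANCOVA cuts variance by 9%, 25% and 49% at ρ = 0.3, 0.5 and 0.7. Compared with a change-score t test, the cuts are 35%, 25% and 15%. The worst case is a loss of about 1% in variance, or 0.3 points of power, when ρ is near 0.

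The direction rests only on randomisation and a usable baseline. The sizes rest on an assumed ρ, which may differ between LVEF and the four markers. The power figures rest also on the assumed 0.5 SD effect, and the change-score figures on equal SDs at the two times. The primary outcome and its chi-square test are untouched.

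**What to change.** In section 2.8, replace the t test for LVEF, ET, NO, IL-6 and CRP with a between-arm ANCOVA. The response is the end-of-treatment value; the terms are arm and the same variable's pre-treatment value. Report the adjusted difference with its 95% confidence interval. Analyse markers with skewed distributions on the log scale, with baseline also logged, and report the result as a ratio. Use the same model at 72 hours as supportive. Fix the choice of model and scale before unblinding.

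The cost is a change of wording and one degree of freedom per model. No extra patients, visits or assays are needed. Each patient must have a baseline value, so the plan should say how a missing one is handled.

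### IL-6 and CRP, likely right-skewed and measured at baseline, are committed to mean ± SD and an unadjusted t test: a minor loss of precision on secondary outcomes

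*Protocol article*

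**What the plan says.** Section 2.8 (Statistical analysis) states that "the measurement data will be expressed by" mean ± SD and tested by t test. Rates go to a chi-square test, and P below .05 means that "the difference is statistically significant". The section has no normality condition, transformation, rank-based alternative or covariate.

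Section 2.6 names the outcomes that fall under the continuous-data rule: "Secondary outcome index: left ventricular ejection fraction (LVEF), endothelin (ET), nitric oxide (NO) level, interleukin-6 (IL--6), C-reactive protein (CRP". The primary outcome is a response rate and is not touched by this point.

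Patients enter when "onset time is within 24 hours" (section 2.3). Under section 2.7, data are collected "before the beginning of treatment, 72 hours after the beginning of treatment and at the end of treatment", so each marker has a pre-treatment value. Section 2.4 gives the size: "One hundred twenty patients will be randomly divided into observation group and treatment group according to the rate of 1:1", that is 60 per arm.

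**The concern.** IL-6 and CRP are concentrations. They cannot fall below zero, and in an acute reaction of widely varying size they can rise many-fold in some patients, so a long right tail is likely. Two things follow for a raw-scale analysis.

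- **Summary.** Once the SD approaches the mean, mean ± SD reaches zero or below and no longer describes a typical patient.
- **Comparison.** A few high values supply much of the variance and widen the interval for the mean difference.

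Separately, a two-sample t test leaves out the baseline value, which usually explains part of the later value. Section 3 (Discussion) rests the rationale partly on an anti-inflammatory action that includes lowering CRP. These markers test that mechanism, so an imprecise comparison could blur a real effect.

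**Working it through.** The article gives no power, effect size, SD or distribution for any marker, so there is no figure to reproduce. The check asks how the stated test compares with a log-scale test under stated assumptions.

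**Inputs from the article:** 60 per arm (120 at 1:1, section 2.4) and alpha 0.05 (section 2.8).

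**Assumptions:** two-sided testing; the CV; a proportional treatment effect (the ratio); the shape of the distribution; and, for the last step, a correlation of 0.5 between baseline and follow-up.

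**1. Summary.** For a lognormal variable, median/mean = 1/√(1 + CV²). At CV 1.0 this is 1/√2 = 0.71, and mean − SD is exactly zero. At CV 1.5 the lower end of mean ± SD is negative.

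**2. Log-scale power by hand, CV 1.0, ratio 0.70.**
- Lognormal: log SD = √ln(1 + CV²) = √ln 2 = 0.833. SE = 0.833 × √(2/60) = 0.152. Signal = |ln 0.70| / 0.152 = 0.357 / 0.152 = 2.35. Power ≈ Φ(2.35 − 1.98) = 64%.
- Gamma with the same CV (an exponential): log SD = π/√6 = 1.283. SE = 1.283 × √(2/60) = 0.234. Signal = 0.357 / 0.234 = 1.52. Power ≈ Φ(1.52 − 1.98) = 32%.

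The gamma shape has a long left tail on the log scale. That is why the log test does badly there.

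**3. Simulated power (20,000 trials per setting), unadjusted t tests.**

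| CV | Ratio | Lognormal: raw | Lognormal: log | Gamma: raw | Gamma: log |
|---|---|---|---|---|---|
| 0.3 | 0.85 | 84% | 85% | – | – |
| 0.5 | 0.75 | 88% | 91% | – | – |
| 0.8 | 0.70 | 69% | 79% | 67% | 55% |
| 1.0 | 0.70 | 51% | 64% | 47% | 33% |
| 1.5 | 0.65 | 39% | 58% | 32% | 16% |

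Lognormal loss for the raw test: 1, 3, 10, 13 and 19 points. Under gamma the raw test is ahead by 12, 14 and 16 points in the last three rows.

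A second lognormal run set the effect so that the log test has 80% power. The raw test then had 77.6%, 74.9%, 67.0%, 60.5% and 53.6% at log SD 0.3, 0.5, 0.8, 1.0 and 1.2 (CV 0.31, 0.53, 0.95, 1.31 and 1.79). The pattern is the same: small at mild skew, large at strong skew.

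**4. Validity and influence.** In the second run the raw t test's type I error fell from 5.1% at log SD 0.3 to 4.3% at 1.2. The three largest of 60 values carried 33% to 67% of an arm's sum of squares.

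**5. Baseline adjustment.** With correlation ρ, the residual variance is multiplied by 1 − ρ². At ρ = 0.5 that is 0.75, so the SE is multiplied by √0.75 = 0.866. At CV 1.0 the signal becomes 2.35 / 0.866 = 2.71, and power ≈ Φ(2.71 − 1.98) = 77%. The simulated lognormal log-scale figures were 65% unadjusted and about 75% adjusted. Adjustment raised power on the same scale in every setting run.

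**The case against.** The strongest objection is that skew alone does not make the log scale better. The lognormal model is the one under which a log-scale t test does best, and a gamma shape with the same CV reverses the ranking. This stands: the power gain is conditional on shape, and at low CV it is negligible even under lognormal data.

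Three further readings are tempting, and the article does not support them.

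- **That extreme values produce false findings.** Type I error stays near or slightly below nominal at 60 per arm. Extreme values mainly inflate the SD and widen the interval.
- **That all four blood markers are affected alike.** The acute-phase argument applies to IL-6 and CRP. Nothing in the article supports strong skew for ET or NO.
- **That sampling is fixed at 72 hours after the infarct.** Section 2.7 has "72 hours after the beginning of treatment", and onset may be up to 24 hours before entry. There is also an end-of-treatment sample at four weeks, when the acute-phase argument is weaker, and no time point is named as the main one.

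A geometric-mean ratio also answers a different question from a mean difference, and a proportional effect is assumed here, not shown. That is a fair cost of the change.

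Finally, a fuller protocol or an SAP, not shown, could add a transformation. The point does not rest on missing detail, though: section 2.8 states a method for all continuous data, and a later transformation would depart from it.

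**Conclusion.** The point holds in a limited form. Section 2.8 commits IL-6 and CRP to a summary that is likely to misdescribe them and to a comparison that ignores a baseline value already being collected. The planned test is valid, and the primary outcome is unaffected.

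The cost depends on quantities that the article does not give. Under a lognormal shape, the loss from staying on the raw scale runs from negligible at low CV to roughly a fifth of the power scale at CV 1.5. Under a gamma shape the raw scale can be the better choice. The gain from baseline adjustment is the steadier part: it does not depend on the choice of scale, but its size depends on the assumed correlation of 0.5.

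Severity is minor, and only secondary outcomes are concerned.

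**What to change.** Amend section 2.8 before unblinding, so that the scale is not chosen from the results:

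- **IL-6 and CRP:** analyse on the log scale with log baseline as covariate, report geometric-mean ratios with 95% CIs, and summarise by median and quartiles.
- **LVEF, ET and NO:** keep the raw scale and add the baseline value as covariate.

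The change takes a sentence or two and needs no new data or patients, since baseline values are already collected. The downside is that IL-6 and CRP results will read as ratios instead of mean differences. If these markers turn out closer to a gamma shape than to a lognormal one, the log scale would give up some power.
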